## Methods

### Study Population

East Sumba District was selected as the study area because it is classified as a high malaria-endemic region [64]. The district consists of 22 subdistricts and 156 villages [65]. The total population in the district is 248,776, with an almost equal distribution of male (51.4%) and female (48.6%) residents. Approximately one-half of the population is engaged in the agricultural sector. The district has 4 hospitals, 22 public health centers, and 78 subsidiary public health centers across the region [65]. This study was conducted in 4 selected subdistricts where there is 1 public health center in each subdistrict, as indicated in Figure 1.

**Figure 1 figure1:**
[figure not shown]
Map of study sites.

### Study Design and Sampling Technique

This study used a cluster-assigned quasi-experimental design with pretest and posttest assessments in both control and intervention groups. The cluster unit for this study was the village, which was not randomized because the research team aimed to implement the intervention across all villages within a selected subdistrict, where the subdistrict leader would serve as a role model to encourage the community to improve malaria awareness. To obtain a representative sample, the research team randomly selected 4 of the 22 subdistricts, of which 2 were assigned as the intervention groups and 2 served as the control groups. The first 3 subdistricts each had 6 villages, and the fourth subdistrict had 7 villages; therefore, a total of 25 villages participated in the study, representing about 16% of all the villages in the district. Of these, 13 villages were assigned to the intervention group, while 12 villages formed the control group. The number of sampled households selected from each village was proportional to the number of households in that village. Within each selected village, households were randomly sampled to serve as an experimental unit as indicated in Figure 2.

**Figure 2 figure2:**
[figure not shown]
Flowchart of the selection of malaria-endemic settings and the village populations. KAP: knowledge, attitude, practice; SD: subdistrict; V: village.

### Sample Size Calculation

To determine the required sample size for the baseline prevalence of study outcomes, the research team applied the Leslie-Kish formula for calculating the sample size in cross-sectional studies [66]:

where n_0_ is the initial sample size; p is the prevalence of malaria awareness in ENT Province (48.8%) [39], Z is the confidence level at 95% (standard value of 1.96), and d is the relative precision (0.05); therefore, the initial sample size was 384 participants. For the population survey, a community correction factor of 2 was applied, doubling the required sample size to 768 participants. Additionally, a 15% buffer was added to account for potential incomplete data, primarily due to nonresponse or failure to complete interviews. Thus, the final sample size was determined to be 884 participants with 442 individuals in the control group and 442 individuals in the intervention group. This number served as a guideline for recruiting participants for the household survey, which was conducted both before and after the intervention.

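### The sample size calculation calls d = 0.05 a relative precision, but 384 follows only from 5 percentage points absolute; the factor of 2 must also be defined before that precision can be attached to the pooled sample or to an arm

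*Protocol article*

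**What the plan says.** The section Sample Size Calculation gives its aim as "To determine the required sample size for the baseline prevalence of study outcomes" and uses a formula for cross-sectional studies. The inputs are a malaria awareness prevalence of 48.8%, Z = 1.96 for 95% confidence, and a precision of 0.05. The precision and the result appear in one sentence: "d is the relative precision (0.05); therefore, the initial sample size was 384 participants".

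Two adjustments follow. First, "a community correction factor of 2 was applied, doubling the required sample size to 768 participants". Second, "a 15% buffer was added to account for potential incomplete data, primarily due to nonresponse or failure to complete interviews". The outcome is that "the final sample size was determined to be 884 participants with 442 individuals in the control group and 442 individuals in the intervention group". The article calls this number a guideline for recruitment to the surveys before and after the intervention. It states no precision for a single arm, no power and no detectable difference.

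**The concern.** Relative and absolute precision are different targets. At a prevalence of 48.8%, 5% relative is a half-width of 0.05 × 48.8 = 2.44 points, while 5% absolute is a half-width of 5 points. The label and the result stand side by side in the article and cannot both be right. A reader who takes the label at face value credits the baseline estimates with about twice the precision that the calculation gives.

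A second question follows once the label is corrected: 5 points for whom? The total is doubled by a factor whose purpose is not given, and is then split into two arms of 442. Depending on what the factor stands for, the 5 points belong either to the pooled sample or to each arm. The Results timeline runs analysis and manuscripts to December 2026, so the wrong description could be carried into the planned papers.

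**Working it through.** **Inputs** (all from Sample Size Calculation): p = 0.488, Z = 1.96, d = 0.05, factor 2, buffer 15%, final total 884, 442 per arm. The printed equation is not visible in the text at hand. The standard single-proportion formula is assumed, and it reproduces the stated result.

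**1. The plan's own figures**
- Absolute d: n = Z² p(1 − p)/d² = 3.8416 × 0.488 × 0.512 / 0.0025 = 383.9, so 384.
- Factor: 384 × 2 = 768.
- Buffer: 768 × 1.15 = 883.2, so 884, or 442 per arm.

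Every stated figure reproduces, with d taken as 5 percentage points absolute.

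**2. The figure that the label implies**
- Relative d: n = Z² (1 − p)/(p d²) = 3.8416 × 0.512 / (0.488 × 0.0025) = 1,612.2, so 1,613 before the factor of 2.
- Ratio: 1,613/384 = 4.2.
- Relative precision that 384 does give: 0.05/0.488 = 10.2%.

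**3. What the 5 points apply to**

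The half-width is 1.96 × √(D × 0.488 × 0.512 / n), where D is the design effect.

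| Meaning of the factor of 2 | Sample | D | Half-width (points) | Relative to 48.8% |
|---|---|---|---|---|
| Design effect | pooled, 768 | 2 | 5.0 | 10.2% |
| Design effect | one arm, 442 | 2 | 6.6 | 13.5% |
| Design effect | one arm, 384 evaluable | 2 | 7.1 | 14.5% |
| Doubling for two arms | one arm, 384 | 1 | 5.0 | 10.2% |

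Under the last reading there is no allowance for clustering, although Study Design and Sampling Technique makes the village the cluster unit, with 13 intervention and 12 control villages.

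**The case against.** **The defect is one wrong word.** The three counts are sound, and nothing suggests that a design of 1,613 or more was ever intended. This stands, and it is why the remedy is a relabelling. It does not remove the point, because the label states a property that the sample does not have.

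**The article never promises 5 points in each arm.** It says openly that it sizes for a baseline prevalence, and a condensed article may leave the meaning of the factor to the full protocol. This stands in part. A reader might infer that the arms fail a stated target. The text does not support that: no per-arm target is given, and if the factor doubles the sample for two arms, each arm has the 5 points. The per-arm widths are therefore conditional. The definition is still needed, because the corrected precision cannot be attached to any group without it.

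**The buffer.** A reader might infer that 884 is too small because 768/0.85 = 904. The article says that 15% was added, which is exactly 768 × 1.15, and it states no 15% loss rate. The gap is 20 people, or 2.3% of 884. Even a 15% loss would leave 751 and a pooled half-width, with a design effect of 2, of 5.05 instead of 5.00 points. This is not an error.

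**Power.** A reader might also infer that the study is too small for the intervention effect, since Statistical Analysis plans comparisons between groups. One can compute a detectable difference in change of about 19 to 20 points: 2.80 × √(4 × 0.488 × 0.512 × 2/n) = 0.187 at n = 447 and 0.202 at n = 384. That rests on a design effect of 2 in each arm and wave, independent waves, p near 0.488 throughout, equal arms, 80% power, and a test of the difference in change. The article states none of these as a basis for sizing. The same villages are surveyed in both waves, so independence may overstate the figure. The article claims no power, and both surveys have already been done.

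**Conclusion.** The precision is wrong as written. With the article's own inputs, 384 corresponds to ±5 percentage points absolute, or 10.2% relative. The stated 5% relative would need 1,613 before the factor of 2. This part rests only on printed inputs and the standard formula.

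The second part is conditional on an undefined term. As a design effect, the factor of 2 gives ±5 points for the pooled baseline prevalence and about ±6.6 points in an arm of 442 (±7.1 at 384 evaluable). As a doubling for two arms, it gives ±5 points in each arm of 384, without allowance for village clustering. The documents do not settle which is meant.

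The point does not extend to a miscounted sample, a short buffer or a failed power claim.

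**What to change.** In Sample Size Calculation:

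1. Replace relative by absolute, and give d as 5 percentage points. The counts 384, 768 and 884 stay as they are.
2. Say what the factor of 2 is, and add the one sentence that follows from it:
   - if it is a design effect, that ±5 points applies to the pooled baseline prevalence and that each arm of 442 has about ±6.6 points (±7.1 at 384 evaluable);
   - if it is a doubling for two arms, that each arm of 384 has ±5 points with no allowance for village clustering.
3. Use the same wording in the planned papers.

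The cost is wording only. The described precision becomes less favourable. No further enrolment, change to the buffer or added detectable difference is asked for.

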### Eligibility Criteria

Individuals were eligible for recruitment if they had resided in the selected villages for at least 12 months and did not intend to migrate or relocate within the next 6 months after initial contact. Furthermore, participants were required to be at least 18 years old. All participants were required to provide written informed consent. For those who were unable to read or write, the consent form was read aloud by trained research assistants (RAs), and participants provided consent using a thumbprint on an ink pad. The RAs graduated from public health degrees and were local nurses with prior experience in data collection and employment at local public health centers. These professionals were recruited to ensure the study’s data collection process was conducted effectively.

### Study Procedure for Malaria Awareness Campaign

This study followed a 4-stage process to achieve its primary outcomes, as described in the following sections.

#### Phase I (Preparation Stage)

During this phase, the research team submitted an application to the Health Research Ethics Commission of Nusa Cendana University Kupang ENT Province, Indonesia, to obtain research ethics approval. Following approval, the research team coordinated with local authorities at various administrative levels, from the provincial level to the village level, in East Sumba District to obtain permission letters for conducting the study in the selected areas.

#### Phase II (Baseline Phase)

After securing the necessary approvals and obtaining the recommendation letter from the relevant authorities, the research team conducted a household survey with both the intervention and control groups. Before data collection, respondents were provided with a general overview of the study, and informed consent forms were obtained before their participation. The survey aimed to assess behavioral aspects of malaria and was conducted using a questionnaire that had been modified from a previous study conducted in rural ENT Province [67]. The questionnaire consisted of 40 questions designed to collect data on key malaria-related behaviors, including general knowledge of malaria, treatment-seeking behavior, and the use of malaria prevention methods. The questionnaire was completed by either the head of the household or another household member aged 18 years or older.

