#### Phase III (Intervention Stage)

In the control group, malaria education for the local community was integrated into routine services at the local health center. These educational sessions were provided during the first prenatal visit by pregnant women to the health center, food supplement distribution activities, and immunization programs conducted during integrated service post activities at the village level. These activities were conducted once per month, and malaria-related information was disseminated once per village on average. The primary audience for these sessions included pregnant women, mothers with children younger than 5 years, and young children. Occasionally, malaria education was provided to all individuals attending the health centers. In the intervention group, malaria education followed the same structure as in the control group but was supplemented with a health education campaign targeting the entire village community.

The intervention followed the steps outlined in the following paragraphs.

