#### Phase IV (Evaluation Stage)

At this stage, the research team conducted a household survey in both the intervention and control groups using the same questionnaire that was administered during the baseline phase of the study. The final data collection was done from the third week of January 2025 to the second week of February 2025. Since the research aims to assess the impact of the intervention on all rural adults, participants surveyed before and after the intervention may differ, depending on respondent availability during the data collection period.

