The third outcome variable in this study is improvement in good MPMK. This improvement will be demonstrated if the percentage of the rural population with good MPMK after the intervention is higher than before the intervention. A good level of MPMK is defined as the ability to correctly answer at least one-half of the total questions in the MPMK section, as indicated in previous studies [41,59]. The level of MPMK will be assessed before and after the intervention in both the intervention and control groups.

The fourth outcome variable is the use of bed nets during the dry season in high malaria-endemic settings. Community behaviors regarding bed net use may exhibit seasonal variations, as individuals may adjust their practices depending on weather conditions [71]. This outcome will be assessed based on the participants’ self-reported responses to a survey question asking whether they slept under a bed net the night before the survey.

The fifth outcome variable in this study is the variation in the use of a bed net in the dry and wet seasons. The literature indicates that bed net use might fluctuate based on seasonal weather conditions, as individuals adapt their malaria prevention behaviors accordingly [71,72]. This malaria awareness campaign began at the end of August 2024, during the dry season, and concluded in the second week of January 2025, which corresponds to the wet season in the study area. The study will examine seasonal differences in bed net use by analyzing responses to 4 key questions from the malaria prevention practice section of the questionnaire. The disparity in bed net use between dry and wet seasons will be assessed for both the intervention and control groups.

The sixth outcome variable in this study is improvement in good MPMP. Improvement will be demonstrated if the percentage of the rural population practicing good MPMP after the intervention is higher than before the intervention. A good level of MPMP is defined as the ability to correctly answer at least one-half of the total questions in the MPMP section, as indicated in a previous study [73,74].

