## Results

The time frame of the project is presented in Table 1.

**Table 1 table1:** Timeline of research phases.

Research phases	January-May 2024	June-July 2024	August 2024-January 2025	February 2025	March 2025-December 2026
Questionnaire and question guide development	✓	—^a^	—	—	—
Ethics approval	—	✓	—	—	—
Training of field workers	—	✓	—	—	—
Household surveys for pretest data	—	—	✓	—	—
Data entry	—	—	✓	—	—
Data analysis	—	—	✓	—	—
Manuscript preparation and submission	—	—	✓	—	—
Intervention in 13 villages	—	—	✓	—	—
Household surveys for posttest data	—	—	—	✓	—
Data entry	—	—	—	—	✓
Data analysis for the final outcome	—	—	—	—	✓
Manuscript preparation and submission	—	—	—	—	✓

^a^Not applicable.

Primary data collection for the baseline survey was conducted between August 2024 and September 2024. A total of 894 rural adults participated in face-to-face interviews in both the intervention and control groups. These participants were drawn from 25 villages across East Sumba District. The intervention commenced in the last week of August 2024 and concluded in the second week of January 2025. The project is currently in the process of drafting multiple research papers, which will be submitted for publication in peer-reviewed journals to disseminate the findings. This study was funded by the Directorate General of Higher Education, Ministry of Education and Culture of the Republic of Indonesia (main contract number: 073/E5/PG.02.00.PL/2024) on June 11, 2024, and an extension contract number from the Research Center of Nusa Cendana University Kupang ENT Province (contract number: 448/UN15.22/SP2H/PL/2024) on June 12, 2024.

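### Which adult answers in each household is left open and may change between the two surveys, yet the stated tests make no allowance for a change in respondent mix

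*Protocol article*

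**What the plan says.** **Selection.** Study Design and Sampling Technique randomises down to the household: "Within each selected village, households were randomly sampled to serve as an experimental unit". Phase II then leaves the person open: "The questionnaire was completed by either the head of the household or another household member aged 18 years or older". Phase IV allows a change of person between waves: "participants surveyed before and after the intervention may differ, depending on respondent availability during the data collection period". The same sentence gives the target population as its reason: "Since the research aims to assess the impact of the intervention on all rural adults".

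**Timing.** In Results: "Primary data collection for the baseline survey was conducted between August 2024 and September 2024". In Phase IV: "The final data collection was done from the third week of January 2025 to the second week of February 2025". Outcome Variables says that the campaign began "during the dry season, and concluded in the second week of January 2025, which corresponds to the wet season in the study area".

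**Routine education, same structure in both arms.** Phase III: "The primary audience for these sessions included pregnant women, mothers with children younger than 5 years, and young children".

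**Success rule and tests.** Under Outcome Variables, an awareness index that is higher after than before is taken to show that the campaign worked. Treatment-seeking, prevention knowledge and prevention practice count as improved on the same after-above-before rule. Under Statistical Analysis, awareness before and after is compared by chi-square within each group. Unpaired t tests, with comparisons within and between groups, are named for these four outcomes. Logistic regression is described as a search for associated factors, and for treatment-seeking only predictors with P below .05 stay in the final model. No group-by-time term is named.

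**The concern.** A random sample of households gives a random sample of adults only if the adult within the household is also chosen by a known rule. Here the choice is left to circumstances, which can change between August-September and January-February. About half of the district's population works in agriculture (Study Population), so a seasonal change in who is at home is plausible. Routine education is aimed mainly at pregnant women and mothers of young children, so respondent type may be related to the outcomes.

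If both links hold, the proportion aware can move between waves without any individual learning anything. An unadjusted before-after test cannot tell this from a campaign effect, and the after-above-before rule is met by any positive movement, significant or not.

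Separately, one adult per household without weighting describes the adults who responded in sampled households, which is narrower than all rural adults.

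**Working it through.** **The plan's own figure.** With p = 0.488, Z = 1.96 and d = 0.05 (used as absolute precision), n0 = 1.96² × 0.488 × 0.512 / 0.05² = 383.94, so 384. Then 384 × 2 = 768, and 768 × 1.15 = 883.2, so 884, or 442 per group. The stated figure reproduces, and this point does not change it.

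**Inputs not in the documents.** They give neither the outcome gap between respondent types nor any shift in mix. Both are assumed below, and the results are illustrations.

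**One arm, before against after, no true effect.**
False change = (outcome gap between types) × (shift in share of a type).
- Low: 0.10 × 0.10 = 0.01, or 1 point.
- Middle: 0.20 × 0.15 = 0.03, or 3 points.
- High: 0.30 × 0.20 = 0.06, or 6 points.

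The chance that a two-sided 5% test shows a significant rise, from 48.8% with 442 respondents per wave, is given below. The last column halves the sample to 221, in line with the plan's factor of 2. With no shift the chance in that direction is 2.5%.

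| False rise | n = 442 per wave | effective n = 221 |
|---|---|---|
| 1 point | 4.8% | 4.0% |
| 3 points | 14.3% | 9.2% |
| 4 points (0.20 × 0.20) | 22% | 13% |
| 6 points | 43% | 24% |

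The shift can equally go the other way and hide a real effect.

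**Between arms, difference in change.**
False effect = gap × (shift in intervention arm − shift in control arm), if the gap is the same in both arms.
- Equal shifts: gap × 0 = 0.
- Differential shift of 5 points with a 20-point gap: 0.20 × 0.05 = 0.01, or 1 point.

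The choice of contrast therefore matters more than the assumed gap. A between-arm difference in change removes the common part of the shift, and adjustment for respondent characteristics can reduce what remains. The stated before-after tests do neither.

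**Population.** If one adult is taken at random from a household with k eligible adults, that adult's chance of selection within the household is 1/k. Unweighted results then give adults in larger households too little weight. Here even the 1/k is not assured, because no random choice is stated.

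**The case against.** The strongest reply is that the control arm already deals with this. Both arms are surveyed in both waves with the same questionnaire and the same enumerators, and between-group comparisons are planned to judge impact. Campaign staff came from the Baing and Mahu health centres. Outcome Variables lists Baing as coastal and Mahu as hilly, with Nggongi (coastal) and Kananggar (hilly) as the other two. Each arm thus appears to have one coastal and one hilly area, which makes very different seasonal patterns less likely. This stands as far as it goes: a common shift cancels in a difference in change. But no such contrast is named, the first outcome is read before against after, and two subdistricts per arm cannot guarantee equal shifts.

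A second reply is that the covariates are collected and regressions are planned, and that a condensed article leaves detail to other documents. The first part is true and makes the remedy cheap. However, the article itself fixes the success rule, the unadjusted tests and the purpose of the regressions, so the point concerns what is stated. The change of respondents is openly disclosed, and unpaired tests suit that design. They do not correct for composition.

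Three stronger readings are tempting, and the documents do not support them:
- *That a seasonal shift has biased the results.* Nothing shows that the mix shifted, and Phase II does not mention availability at baseline.
- *That the campaign effect is off by 1 to 6 points, as much as the design precision of 5 points.* The range is a single-arm change from assumed inputs. The 5 points is the precision of one prevalence estimate, not of a change or a between-arm contrast.
- *That the routine education implies a large gap between women and men.* Phase III says malaria information was given about once per village on average, and occasionally to everyone attending. A gap is plausible, but its size is unknown.

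**Conclusion.** The concern holds as a risk. The responding adult is not selected by rule and may change between a dry-season and a wet-season wave. The stated tests are unadjusted, and for awareness a rise is read as a campaign effect, so a change in respondent mix could pass for an effect or mask one. Size and direction cannot be derived from the documents. Under the assumptions shown, the false change is 1 to 6 points in a single-arm comparison and about 1 point in a between-arm difference in change with a modest differential shift. Independently of any seasonal shift, a claim about all rural adults is wider than the respondent rule supports. The point calls for an inexpensive improvement to the analysis. It does not show that the study's results are invalid.

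**What to change.** 1. State the campaign comparison as the between-arm difference in change (a group-by-time term), adjusted for sex, age group, education and occupation. All four are listed under Independent Variables. Keep them in the model whatever their P value.
2. If results are standardised instead, use one common mix for every arm and wave, such as the pooled baseline sample. The 51.4% male figure in Study Population would be a poor standard: it covers the district's whole population at all ages, not rural adults.
3. Tabulate respondent characteristics by arm and wave. This will show whether the measured mix changed.
4. Describe the population as responding adults of sampled households, unless results are weighted by the number of eligible adults. The article lists family size as a variable. Whether the number of adults was recorded cannot be seen from it.

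The cost is some rewording and a little more analysis of collected data, slightly wider intervals and a narrower population statement. The timeline places the final analysis between March 2025 and December 2026. Adjustment covers only measured characteristics, so some difference in who was available may remain.
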